## 3.0 OBJECTIVES

## 3.1 Primary Objective

The primary objective of the study is to compare the safety of Acidform lubricant to HEC gel by assessing the genital tract mucosal response to 14 days of twice daily application by measuring endogenous antimicrobial activity and levels of mediators of host defense, including defensins, cytokines, and chemokines in CVL.

**3.2 Secondary Objective**

To assess the extent and duration of buffering by measuring vaginal pH prior to and 2 hours after the first application of Acidform or HEC.

**3.3 Exploratory Objectives**

To determine whether intravaginal application of Acidform lubricant or HEC results in changes in epithelial integrity by collecting cervical biopsies.

To evaluate changes in vaginal flora following repeated intravaginal application of Acidform lubricant or HEC.

To examine the antiviral activity in CVL collected 2 hours following a single dose application of Acidform lubricant or HEC gel using a spiking strategy.

**4.0 STUDY DESIGN**

This is an open-label randomized comparative study of Acidform lubricant and HEC gel to be conducted among 36 women at 2 clinical sites, the Albert Einstein College of Medicine (AECOM) and Montefiore Medical Center (MMC). The female participants will have a normal gynecological history and be at low risk for HIV or other STI. Participants will be randomized to apply Acidform or HEC twice daily for 14 consecutive days between menses. Instead Healthcare, LLC (La Jolla, CA) will provide Acidform lubricant and HEC gel. The randomization will be 1:1 (i.e., 18 in each treatment arm). Participation in this study will last approximately two months.

Prior to screening, potential participants will be informed of the need to abstain from insertion of anything into their vagina from 48 hours prior to the enrollment visit until completion of the study. Women unwilling or unable to assure abstinence will not be enrolled. Participants must agree to abstain from vaginal or anal intercourse or insertion of sexual toys. They must also agree not to douche or use any vaginal product other than the investigational product including lubricants, feminine hygiene products, and vaginal drying agents for 48 hours before enrollment and for the duration of the study (21 days).

At the screening visit, eligible volunteers will come to the General Clinical Research Center (GCRC) at the AECOM or MMC. After informed consent is obtained for the study and for HIV testing, a medical, gynecological, and sexual history will be obtained. Urine will be collected for microscopy, culture, and a pregnancy test. If the pregnancy test is negative, a pelvic examination will be performed including a speculum exam with visual inspection, pH measurement, wet mount, and collection of a baseline cervicovaginal lavage (CVL) sample. CVL is a wash of the cervicovaginal area using 10 ml of normal saline. A 10 ml syringe filled with saline is aimed directly at the cervical os and posterior vaginal wall. The pooled fluid is aspirated and the volume is collected. A Pap test will be performed if documentation of a negative result within the last year is not available. A cervical swab for nucleic acid amplification testing for *N. gonorrhoeae* and *C. trachomatis* will be done. One biopsy will be obtained from the ectocervix near the external os. [name] or [name] will collect the cervical biopsy colposcopically. If there is evidence of a clinically detectable genital abnormality (i.e., ulcer, lesion or positive wet mount) or urinary tract infection, appropriate treatment and follow-up will be provided and the volunteer will be ineligible to continue in the study at this time. If a lesion or ulcer is present at this or any visit, a herpes culture will also be performed. Blood will be collected for a pregnancy test, HIV EIA, RPR, HSV serologies (type common and type-specific; Focus Technologies, Herpes Select) (See Appendix I). Subjects with no contraindications to study participation will be presumed eligible for enrollment.

On the day of Enrollment (Day 0) (2-6 days after the next menses, within 30 days of screening), participants will return to the GCRC. Test results from screening will be reviewed. Urine will be collected for a repeat pregnancy test. If the pregnancy test remains negative, a speculum exam will be performed and the vagina and cervix will be visually inspected. A pH sample from the vaginal wall and a gentle swab for wet mount will be obtained. A vaginal swab will be collected for assessment of vaginal flora and a cytobrush will be obtained to measure immune cell populations. If there is evidence of a clinically detectable genital abnormality (i.e., ulcer, lesion or positive wet mount) appropriate treatment and follow-up will be provided and the participant will be ineligible to participate further at this time. If there is evidence of recent intercourse (sperm visualized on wet mount or positive p30 test), the participant will be ineligible to continue in the study. If the patient is eligible, participants will be randomized to receive Acidform lubricant or HEC gel. The participant will insert one dose of study gel intravaginally under the guidance of the study clinician. A repeat pelvic exam with visual inspection, measurement of vaginal pH and collection of CVL will be performed 2 hours after application of Acidform or HEC gel. Provided that the first dose is well tolerated, the participants will insert subsequent applications twice daily for 13 consecutive days (preferably in the morning and at bedtime) (see Appendix III). Subjects will be instructed and frequently reminded to apply one dose in the morning and a second dose at bedtime. Study gels will be provided in single-use tubes with separate vaginal applicators and the participant will be provided with a study diary to record usage, symptoms and reasons for non-adherence.

Every effort will be made to bring participants back after 7 and 14 doses of Acidform or HEC. Visits will be scheduled in the GCRC on Day 7 (range, days 5-9) and Day 14 (range, days 12-15). For study visits conducted on Day 7 and 14, subjects will be instructed to apply the morning dose after the study visit is completed. There will be a Final Visit scheduled on Day 21 (range, days 16-21), prior to the anticipated onset of menstruation. A pelvic exam will be performed and vaginal pH will be measured at each visit. CVL samples will be obtained at the Screening Visit, Enrollment Visit (2 hours after the application of Acidform or HEC), and on Days 7, 14, and 21. A cytobrush for measurement of immune cell populations and a vaginal swab for assessment of vaginal flora will be collected at Enrollment (prior to application of Acidform or HEC), Day 14 and Day 21. [name] or [name] will collect one cervical biopsy colposcopically at the Day 14 visit for assessment of epithelial integrity. Participants will be instructed to document symptoms of vulvar or vaginal soreness or pruritus, vaginal bleeding, dysuria, or acts of vaginal penetration in a study diary, which will be provided. Participants will be asked to record information on the number of times they administer study gel, time of each insertion, emergence/resolution of specific symptoms and reasons for non-adherence. Diaries will be reviewed at each visit. Participants will bring used and unused supplies with them to each visit for counting and disposal. Adverse events will be recorded as described in Section 8.0. Subjects will receive $25 at the Screening visit. An additional $25 will be given at Screening if a biopsy is performed. Fifty dollars will be provided at the Enrollment, Day 7, Day 14 and Day 21 study visits. An additional $50 will be given for completion of a biopsy at the Day 14 study visit. A total of $300 will be provided for completion of all study visits as compensation for their time and travel expenses.

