We recently completed a pilot study to compare endogenous anti-HSV activity and levels of immune mediators in CVL from women who were naturally cycling (n=9) to women receiving hormonal contraception (n=7). We found that women receiving hormonal contraception had decreased intrinsic anti-HSV activity compared to cycling women. In our 14-day PRO 2000 study, women who were naturally cycling had lower levels of several mediators of mucosal immunity mid-cycle and during the proliferative phase relative to women using hormonal contraception (11). Given the limited data on the effect of reproductive hormones on mucosal immunity, we will limit enrollment to naturally cycling women to assess the impact of Acidform application on endogenous antimicrobial activity and mucosal immune mediators.

This study also builds on our previous work in which we tested the antiviral activity in CVL collected after a single application of 0.5% PRO 2000 gel or matched placebo using a spiking strategy (12). We found that CVL obtained 1 hour after a single application of 0.5% PRO 2000 gel significantly inhibited HIV and HSV infection *in vitro* at least 1000-fold, indicating that the drug is sufficiently bioavailable and retains substantial antiviral activity after intravaginal application. However, the antiviral activity was reduced if virus was introduced diluted in human seminal plasma (13). In the proposed study, we will measure the antiviral activity provided by Acidform by collecting CVL post-application and spiking with primary isolates representing different clades with virus diluted in seminal plasma.

Although the precise mechanisms by which HIV and other STI pathogens gain access to their target cells has not been fully elucidated, the epithelium provides an important first line of defense. Virus must overcome the protective multilayered vaginal epithelium and the tight junctions between epithelial cells, which provide a relatively impervious barrier to HIV-1 target cells, which include dendritic cells, T cells and macrophages. The epithelial barrier and tight junctions may be disrupted in the setting of other STI or following exposure to hyperosmolar vaginal products or microbicides (14). The importance of this barrier is highlighted by recent *in vitro* and murine studies from our lab.

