# 5.1 Participant Inclusion Criteria

# Women who meet all of the following criteria (by self-report, unless otherwise specified) are eligible for inclusion in this study:

- Age between 18 and 50.
- Able and willing to provide written informed consent to participate in the study.
- Normal menstrual history with regular cycles with a minimum of 21 days between menses.
- Low risk for HIV/STI infection. Low risk is defined as

1. Not having had an STI in the last 6 months.
2. Not having used non-therapeutic intravenous drugs in the last year.
3. Being either sexually abstinent or being in a stable, mutually monogamous relationship with a partner who is not known to be HIV positive.

- Agree to the insertion of Acidform lubricant or HEC gel.
- Agree to abstain from vaginal and anal intercourse and to not use vaginal products for 48 hours prior to enrollment and for the duration of the study (through the Final Visit).

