# 5.2 Exclusion Criteria

Women who meet any of the following criteria (by self-report, unless otherwise specified, at screening, enrollment, or at anytime during participation, unless otherwise specified) will be excluded from this study:

- Are pregnant (based on a serum or urine pregnancy test) or less than 6 months post-partum.
- Are currently breastfeeding.
- Are menopausal.
- Are currently using hormonal contraception or have used hormonal contraception in the previous 2 months.
- Are currently menstruating (at screening or enrollment visits – may be eligible for deferment).
- Are currently participating in a research study of other vaginal products.
- Have a positive HIV test at screening.
- Have a urinary tract infection at screening (may be eligible for re-screening after treatment).
- Have a positive chlamydia, gonorrhea, or trichomonas result at screening.
- Have an abnormal Pap test (if documentation of a negative result within the past year is not available).
- Have a clinically detectable genital abnormality (i.e., vulvar, vaginal, cervical and/or perianal ulcer and/or lesion or an abnormal wet mount).
- Have a history of intermenstrual bleeding in the 3 months prior to enrollment.
- Have had gynecological surgery or received treatment for syphilis, genital herpes, chlamydia, gonorrhea, trichomonas, or genital warts in the last 6 months.
- Have received treatment for candida, bacterial vaginosis, or urinary tract infection in the prior month.
- Have douched or used any vaginal products**,** including lubricants, feminine hygiene products, vaginal drying agents and sex toys during the 48 hours prior to enrollment.
- Have had vaginal or anal intercourse during the 48 hours prior to enrollment.
- Oral or intravenous antibiotics in the 7 days prior to enrollment.

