## Screening Visit

## Clinical Procedures

- Obtain informed consent.
- Assign Participant ID.
- Collect demographic and locator information.
- Collect medical history and concomitant medication information.
- Collect blood for pregnancy test, HIV EIA, RPR, herpes serology
- Collect urine for HCG pregnancy test; provide participant with result.
- Collect urine for microscopy and culture.
- Perform pelvic examination including:
- Speculum examination of vagina and cervix,
- Collection of pH sample from the vaginal wall, anterior and posterior fornices,
- Swabs from anterior or lateral fornix for wet mount (two samples of discharge on slide for saline prep, potassium hydroxide prep and whiff test), & p30 test for detection of semen (One-Step ABA card PSA, Abacus Diagnostics, West Hills, CA).
- Collection of baseline CVL,
- Pap test (if documentation of a negative result within the past year is not available),
- Cervical swab for *N. gonorrhoeae* and *C. trachomatis*,
- If ulcerative lesions are noted, collect swab for herpes simplex virus culture,
- Colposcopically directed cervical biopsy.
  - If participant determined to be ineligible, end visit and complete all required data collection forms. If participant remains presumptively eligible, schedule Enrollment Visit to occur 2-6 days following menses within 30 days after the Screening Visit.
- Instruct participant not to use vaginal products and to abstain from vaginal and anal intercourse for 48 hours prior to the Enrollment Visit.
- Complete all required data collection forms.

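### The only untreated CVL and biopsy are taken at Screening, outside the 48-hour abstinence and no-product rules, so the baseline can carry semen or product residue

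*Protocol*

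**What the plan says.** **Sampling.** Section 4.0 of the protocol lists every lavage: "CVL samples will be obtained at the Screening Visit, Enrollment Visit (2 hours after the application of Acidform or HEC") and Days 7, 14 and 21. Before the first dose at Enrollment, only a flora swab and a cytobrush are taken. Section 7.1 sends the 2-hour CVL to the spiking studies. The untreated CVL therefore comes from Screening alone, and so does the untreated biopsy (Appendix I). Enrollment follows within 30 days.

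**Abstinence and product rules.** All are anchored to Enrollment:
- Section 4.0 asks women "to abstain from insertion of anything into their vagina from 48 hours prior to the enrollment visit until completion of the study", and bars products such as "feminine hygiene products, and vaginal drying agents for 48 hours before enrollment and for the duration of the study (21 days").
- The inclusion criterion in Section 5.1 reads "Agree to abstain from vaginal and anal intercourse and to not use vaginal products for 48 hours prior to enrollment".
- The exclusion criterion in Section 5.2 reads "Have had vaginal or anal intercourse during the 48 hours prior to enrollment".
- In the Screening procedures of Section 7.1, the instruction comes after the CVL and looks forward: "Instruct participant not to use vaginal products and to abstain from vaginal and anal intercourse for 48 hours prior to the Enrollment Visit".

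Section 5.1 admits women in a stable, mutually monogamous relationship as well as abstinent women.

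**Semen testing.** The p30 test is run at Screening (Section 7.1, Appendix I), but the consequence is written only for Day 0: "If there is evidence of recent intercourse (sperm visualized on wet mount or positive p30 test), the participant will be ineligible to continue". Section 5.2 contains no such criterion. Sperm is a listed wet-mount target at Enrollment but not at Screening.

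**Use of the sample.** Section 10.1 adjusts the ANCOVA of antimicrobial activity and mediators for baseline. It also compares the arms by Wilcoxon test on change in percentage reduction of infection, with screening CVL titers as the reference.

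**The concern.** Samples on Days 7, 14 and 21 are taken under enforced abstinence and without other products. The sample they are judged against need not be. A woman may have had intercourse or used a lubricant or douche shortly before Screening and still satisfy every written criterion.

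Elsewhere the protocol treats residue as a problem. Morning doses on Days 7 and 14 are held until after sampling to keep residual gel out of the specimens. Section 2.1 gives seminal plasma a pH of about 8.2 and reports that it reduced the antiviral activity of another gel. The same care is not extended to the baseline.

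Two things are at stake. Noise in the baseline weakens it as a covariate and enters change from Screening in full. A within-arm change can also mix the effect of the gel with the disappearance of semen or product. Collection conditions are fixed by the protocol, and no later analysis can recover a clean baseline.

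**Working it through.** **1. The plan's own figure.** Section 10.2 gives sd 28, margin 28, true difference 0, 18 per arm and 80% power. It states no alpha; 0.05 per side is assumed here.

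n per arm = 2 (sd/margin)² (z₀.₉₅ + z₀.₉₀)² = 2 × 1 × (1.645 + 1.282)² = 17.1, so 18.

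The figure reproduces. At n = 18 the standard error is 28√(2/18) = 9.33. Power is 2Φ(28/9.33 − 1.645) − 1 = 82.5% by normal approximation, or 80.7% by t-based simulation. (At 0.025 per side, 22 per arm would be needed, so 0.05 is the level that fits the plan.) This calculation uses the raw sd and takes no credit for baseline adjustment.

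**2. A contamination model.** The documents give neither the baseline-to-follow-up correlation ρ, nor the share f of women with a contaminated Screening sample, nor the size c of the shift in SD units. All three are assumptions. With contamination independent of the true value:

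- Added baseline variance: e = f(1 − f)c²
- ANCOVA residual variance: 1 − ρ²/(1 + e), in SD²
- Variance of change from Screening: 2(1 − ρ) + e, in SD²

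For f = 20% and c = 1, e = 0.2 × 0.8 × 1 = 0.16. For f = 30% and c = 1.5, e = 0.3 × 0.7 × 2.25 = 0.4725.

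At ρ = 0.5:

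- ANCOVA: 1 − 0.25 = 0.75; 1 − 0.25/1.16 = 0.78; 1 − 0.25/1.4725 = 0.83.
- Change: 1.00; 1.16; 1.47.

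**3. Range over ρ** (clean → 20% at 1 SD → 30% at 1.5 SD):

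| ρ | ANCOVA residual variance | ANCOVA equivalence power, n = 18 | Change-score variance |
|---|---|---|---|
| 0.3 | 0.91 → 0.92 → 0.94 | 87% → 86% → 85% | 1.40 → 1.56 → 1.87 |
| 0.5 | 0.75 → 0.78 → 0.83 | 93% → 92% → 90% | 1.00 → 1.16 → 1.47 |
| 0.7 | 0.51 → 0.58 → 0.67 | 99% → 98% → 96% | 0.60 → 0.76 → 1.07 |

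Power uses the normal approximation with margin 28 and 0.05 per side. In this model a useless covariate returns ANCOVA to variance 1.00, which is the unadjusted case in step 1.

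**4. Within-arm change.** The expected baseline shift is f × c: 0.2 × 1 = 0.20 SD, up to 0.3 × 1.5 = 0.45 SD. On the percentage-inhibition scale that is 0.20 × 28 = 5.6 to 0.45 × 28 = 12.6 points. It appears as change from Screening in each arm without any gel effect. Its expectation is the same in both arms, because the sample precedes randomisation.

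**The case against.** The strongest reply is that the primary objective compares arms, and randomisation protects that comparison. This stands: contamination before allocation is balanced in expectation, with only chance imbalance at 18 per arm. The sample-size calculation also never relied on the baseline, so a noisier covariate gives up a gain that was not counted.

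There are partial safeguards. Women hear of the abstinence requirement before Screening, a sexual history is taken, and p30 (detectable for up to 2 days, per Section 6.4) would flag recent semen. None of these extends the rule to Screening. No action follows a positive result there, and nothing tests for recent product use. The Protocol Summary describes the population as sexually abstinent, but Section 5.1 admits women with a partner and starts the abstinence agreement 48 hours before Enrollment.

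Three stronger readings are tempting, and the documents do not support them:

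- **A serious loss of power.** A reader might compute equivalence power on change from Screening and find a steep fall. Section 10.2 plans equivalence on percentage inhibition with the raw sd, and Section 10.1 names a Wilcoxon test for change. The correlations needed are not in the protocol.
- **Within-arm changes that mean nothing.** They are confounded to an unknown degree, but the HEC arm remains a concurrent control. The clinical adverse-event endpoint uses no baseline at all.
- **A cycle-phase mismatch that calls for a cycle-day covariate.** Section 2.1 says "women who were naturally cycling had lower levels of several mediators of mucosal immunity mid-cycle and during the proliferative phase", but its comparator is women using hormonal contraception. That only hints at a phase effect within women. Section 10.2 reports the same sd of 28 at the initial visit and across all 52 samples from the cycling women. The post-dose visits run from Day 5 to Day 21, so no single baseline day could match them all.

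**Conclusion.** The gap is real and modest. The sole untreated CVL and biopsy fall outside the 48-hour rules, and a positive Screening p30 leads nowhere. The arm comparison is not systematically biased, the sample size is unaffected, and modelled ANCOVA power is at least 85% in every case shown, given 0.05 per side.

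The cost falls mainly on change from Screening. At ρ = 0.5 its variance rises by 16% to 47%, against about 5% to 11% for the ANCOVA residual (0.78/0.75 and 0.83/0.75, before rounding). Within-arm change could also be displaced by 0.20 to 0.45 SD. These sizes depend on assumed ρ, f and c. The variances are a means-based guide to the Wilcoxon analysis, not a calculation for it. That the contamination can occur rests on the protocol text alone.

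**What to change.** In Sections 4.0, 5.2 and 7.1, apply the existing 48-hour abstinence and no-vaginal-product rule before the Screening CVL and biopsy as well as before Enrollment, and give the instruction when the Screening appointment is booked. Add sperm to the Screening wet-mount targets. State that if sperm or p30 is positive at Screening, the CVL and biopsy are postponed until the rule is met.

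The cost is wording, one extra recruitment instruction and a few postponed Screening visits. No participants or assays are added, since p30 and the wet mount are already done at that visit.

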### Laboratory Procedures

- Record results of serum and urine pregnancy tests.
- Record results of urine microscopy and culture.
- Record vaginal pH measurements.
- Examine wet mount by direct microscopy to detect *T. vaginalis*, *C. albicans* infections, and clue cells for BV. Perform whiff test.
- Conduct p30 test for detection of semen.
- Conduct tests for *N. gonorrhoeae* and *C. trachomatis*.
- Read and record Pap test results.
- Conduct culture of swab for HSV, if clinically indicated.
- Conduct serology for RPR with confirmation by FTA-ABS or TPHA for *T. pallidum.*
- Conduct type-specific herpes serology.
- Conduct EIA test for HIV.
- Process, spin, measure volume, aliquot and freeze CVL supernatants, which will be used for assessment of endogenous antimicrobial activity, cytokines, chemokines and mediators of mucosal immunity.
- Process cervical biopsy tissue for assessment of epithelial integrity by microscopy and qRT-PCR.

Enrollment Visit (Day 0)

Participants who are found to be presumptively eligible at their Screening Visits will complete Enrollment Visits within 30 days after the Screening Visit. In order to ensure a minimum of 21 days without menstrual bleeding, participants will be scheduled for an Enrollment Visit 2-6 days after the next menstrual period ends. Participants who do not complete an Enrollment Visit within 30 days of screening must repeat the screening process in order to participate. All participants will receive their screening test results at their Enrollment Visits. For those whose test results meet the study eligibility criteria, the procedures below will be undertaken in a step-wise manner to confirm eligibility. As was the case at the Screening Visit, the procedures will be discontinued if ineligibility is determined at this visit.

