## 10.0 STATISTICAL CONSIDERATIONS

## 10.1 Overview and Statistical Designs Issues

## All subjects who receive treatment (Acidform lubricant or HEC placebo gel) will be included in all analyses. The primary objective of this study is to compare the safety of Acidform lubricant to HEC gel by assessing the genital tract mucosal response to 14 days of twice daily application by measuring endogenous antimicrobial activity and levels of mediators of host defense, including defensins, cytokines and chemokines in CVL. The clinical safety of Acidform when administered twice daily for 14 consecutive days will be assessed by also including the following endpoint: Grade 2 or higher adverse experiences judged by the Investigator to be possibly, probably, or definitely related to product use.

Differences between groups with respect to age and baseline amounts of immune mediators will be compared by *t* test. Differences between groups with respect to endogenous antimicrobial activity of CVL against HSV and *E. coli* and change in mucosal immune mediators will be compared by analysis of covariance and adjusted for baseline (after log transformation of data for cytokines, chemokines, and mucosal mediators). Differences between groups with respect to change in percentage reduction in viral or bacterial infection after application of drug or placebo gel relative to titers in screening CVL samples will be determined by Wilcoxon nonparametric test (with exact p-values).

All visits in which a woman has been exposed to the study product will be included in the analysis of clinical safety. The number and the percentages of participants experiencing at least one Grade 2 or higher AE, and the number and percentage experiencing each specific AE will be tabulated by study arm. Each participant will contribute once in each category (i.e. only for highest severity AE for each participant) for the calculation of event rates. The number and percentage of participants experiencing a Grade 2 or higher AE will be tabulated by severity and relationship to treatment for each treatment group. AEs that lead to study product discontinuation will be listed in a separate data listing. The number and percentage of participants with a Grade 2 or higher AE judged possibly, probably or definitely related to study treatment will be summarized and compared for each treatment group by Fisher’s exact test.

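### The only pre-gel CVL and biopsy are taken at Screening, the one CVL visit outside the abstinence and vaginal-product window, and a positive Screening p30 test has no stated consequence

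*Protocol*

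**What the plan says.** Sampling. Section 4.0 states: "CVL samples will be obtained at the Screening Visit, Enrollment Visit (2 hours after the application of Acidform or HEC"), and then on Days 7, 14 and 21. Biopsies are taken at Screening and Day 14. Section 4.0 and the Section 7.1 Screening list call the Screening CVL the baseline.

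Abstinence and products. Section 4.0 asks participants to "abstain from insertion of anything into their vagina from 48 hours prior to the enrollment visit until completion of the study". The Section 7.1 Screening list looks forward in the same way: "Instruct participant not to use vaginal products and to abstain from vaginal and anal intercourse for 48 hours prior to the Enrollment Visit". The matching Section 5.2 exclusion is "Have had vaginal or anal intercourse during the 48 hours prior to enrollment", with a parallel 48-hour item for douching and vaginal products. Section 5.1 admits women in a stable, mutually monogamous relationship as well as abstinent women.

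Antibiotics. Section 5.2 excludes "Oral or intravenous antibiotics in the 7 days prior to enrollment". Separate items exclude treatment for candida, bacterial vaginosis or urinary tract infection in the prior month, and for listed STIs in the last 6 months.

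Semen detection. The Screening laboratory list includes "Conduct p30 test for detection of semen". The consequence appears in Section 4.0 for Enrollment only: on "evidence of recent intercourse (sperm visualized on wet mount or positive p30 test), the participant will be ineligible to continue in the study". The Screening wet-mount list names trichomonas, candida and clue cells but not sperm. The Enrollment and later lists add sperm, and Appendix II gives sperm as a wet-mount target without naming a visit.

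Analysis. Section 10.1 adjusts the between-group ANCOVA for baseline. It compares change in percentage reduction "relative to titers in screening CVL samples" by an exact Wilcoxon test.

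**The concern.** The protocol protects its follow-up samples with some care. Women abstain, vaginal products are barred, and the morning dose is held back before the Day 7 and Day 14 visits so that residual gel does not affect the samples. The sample against which those visits are read has no comparable protection. A woman in a monogamous relationship may attend Screening soon after intercourse, or after using a lubricant or douche, and her CVL still becomes her baseline. She may also be taking an antibiotic for a reason that Section 5.2 does not list.

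The protocol itself treats semen as relevant. Section 2.1 reports that seminal plasma has a pH near 8.2 and that it reduced the antiviral activity of another gel. Section 6.4 describes p30 as a glycoprotein in semen, and Section 4.1 reports mediators per mg of CVL protein, so semen could also enter the denominator. At stake are the quality of the baseline covariate, the reading of change from Screening within each arm, and the comparability of the pre-gel biopsy with the Day 14 biopsy.

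**Working it through.** 1. Visits set side by side, from Sections 4.0, 5.1, 5.2, 6.4 and 7.1 and Appendix I:

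| Visit | CVL | Biopsy | Inside abstinence/product window | p30 run | Stated consequence of sperm or p30 |
|---|---|---|---|---|---|
| Screening | pre-gel | pre-gel | no | yes | none |
| Enrollment | 2 h after gel | none | yes | yes | ineligible |
| Day 7 | yes | none | yes | yes | recorded; product stopped after more than one lapse |
| Day 14 | yes | yes | yes | yes | as Day 7 |
| Final | yes | none | yes | yes | recorded |

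Screening is the only row without the window and without a consequence, and it supplies the baseline.

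2. Could other text close the gap?
- The Protocol Summary describes the population as sexually abstinent, but Section 5.1 dates abstinence from 48 hours before Enrollment.
- Section 5.2 opens by applying its criteria at screening, enrollment or any time unless otherwise specified. The intercourse, product and 7-day antibiotic items do specify otherwise.
- Section 4.0 excludes for a positive wet mount at Screening. In its Enrollment paragraph, however, it treats sperm and p30 separately from a positive wet mount.
- Section 6.4 says p30 is detectable for at most 2 days. A menses falls between Screening and Enrollment, so the Enrollment test cannot reveal semen in the Screening sample.

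3. The plan's own figure. Section 10.2 gives sd 28, margin 28, 18 per arm and 80% power for equivalence, with no alpha stated. Assuming two one-sided tests at 0.05 each and a true difference of zero, n = 2 × [(1.645 + 1.282) × 28/28]² = 17.1, so 18 per arm. Power at 18 is 82.5% by the normal approximation and 80.7% using the t distribution. The figure reproduces. It uses the sd at a single visit and no baseline adjustment.

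4. Illustration only. Let f be the share of contaminated Screening samples, c the shift in sd units and ρ the clean baseline/follow-up correlation. None of these is in the documents.
- Baseline variance factor: v = 1 + f(1 − f)c².
- Observed correlation: r = ρ/√v.
- ANCOVA residual sd: 28√(1 − r²).
- Sd of change from Screening: 28√(1 + v − 2ρ).

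For ρ = 0.5:
- Clean: residual sd 28√0.75 = 24.2; change sd 28.0.
- f = 0.10, c = 1: v = 1.09, r = 0.479, residual sd 24.6, change sd 29.2.
- f = 0.25, c = 2: v = 1.75, r = 0.378, residual sd 25.9, change sd 37.0.

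Over the same range of f and c, the residual sd goes from 26.7 to 26.8-27.3 at ρ = 0.3, and from 20.0 to 20.8-23.8 at ρ = 0.7. It stays below 28 throughout.

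**The case against.** The strongest reply is that the planned tests compare groups and that Screening precedes randomisation. Semen or product at Screening is then equally likely in both arms and cancels in expectation. This stands. A reader might infer that the Acidform-HEC comparison is biased by removing semen between Screening and follow-up. The documents do not support that, because the confusion of gel effect with abstinence applies to change within an arm.

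A reader might also infer that the trial loses its stated power. Section 10.2 sized it on the unadjusted sd of 28, and the ANCOVA residual sd stays below 28 in every scenario above. What is lost is part of a gain that the sample size never counted. The sd of change can exceed 28, but Section 10.2 does not size the trial on change.

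Chance imbalance is likewise not bias. If four more women in one arm were affected, the mean difference in change would move by 4/18 × 28 = 6.2 points, or 4/18 × 56 = 12.4 for a 2-sd shift. The ordinary standard error is 28 × √(2/18) = 9.3 points. Such imbalance is part of the sampling variation that the tests already allow for.

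Three further points are fair. The seminal-plasma findings in Section 2.1 concern Acidform's buffering and the activity of a different drug, not endogenous CVL activity, so they do not support any particular shift. Section 10.2 does not say that the pilot women abstained, so the sd of 28 may already contain some contamination. Section 5.2 covers treatment for the common genitourinary infections, which leaves only antibiotics taken for other reasons. Appendix II makes the missing sperm entry partly an inconsistency between lists. None of this supplies a Screening condition on intercourse or products, or an action on a positive Screening p30.

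**Conclusion.** The point holds as a gap in how the baseline is collected. The Screening CVL and biopsy are the only pre-gel specimens, and Screening is the only CVL visit outside the abstinence and product window. The general antibiotic look-back does not reach it, and the p30 result obtained there triggers no stated action. The consequences are added noise, a weaker baseline covariate, distorted within-arm change from Screening, and a reference sample not comparable in collection with follow-up. Neither systematic bias between arms nor loss of the stated 80% power is shown.

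The documents give neither the frequency nor the effect of semen at Screening, so the size is unknown. Under the assumed 10-25% prevalence, 1-2 sd shift and correlation of 0.5, ANCOVA residual variance rises by a factor of 1.03 to 1.14: (1 − 0.479²)/0.75 to (1 − 0.378²)/0.75. This is a modest weakness that is cheap to remove. The case for removing it rests on the visit schedule, not on these figures.

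**What to change.** 1. In Sections 4.0, 5.1, 5.2 and 7.1, apply the existing 48-hour no-intercourse and no-vaginal-product condition, and the existing 7-day antibiotic look-back, to the Screening visit as well as to Enrollment. Tell women when the Screening appointment is booked.
2. Add sperm to the Screening wet-mount list in Section 7.1, in line with Appendix II.
3. State that the Screening wet mount and p30 are read before the CVL and biopsy. If sperm or p30 is positive, both samples are deferred and the visit is rebooked.

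No new test is needed. Both tests are already done at Screening, Appendix II places them at the GCRC, and the Section 7.1 list puts the swabs ahead of the CVL and biopsy. The cost is protocol wording, a sentence in the booking call, a short wait for the p30 result and a few rebooked Screening visits. A sensitivity analysis without any baseline that still proves semen-positive can be left to the SAP.
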